## Abstract

**Supplementary Information:**

The online version contains supplementary material available at 10.1007/s00277-024-05867-w.

## Introduction

Development of Janus-kinase inhibitors has revolutionized the therapeutic landscape for patients with myeloproliferative neoplasia (MPN). Following approval of the first Jak1/2-inhibitor Ruxolitinib (Rux), symptoms of this inflammatory disease, characterized by splenomegaly, release of inflammatory cytokines and appearance of thrombosis, could be effectively reduced for the first time [1]. However, JAK-inhibitor treatment is limited in several aspects: (i) duration of response: 3 years after treatment more than 50% of patients have discontinued JAK-inhibitor treatment due to lack of efficacy or resistance [2, 3]. (ii) reduction of disease burden: while effective in reducing inflammation and constitutional symptoms, JAK-inhibitors fail to reduce the malignant clone in the majority of patients and therefore lacks long-term efficacy [4].

Clinical trials for patients with myelofibrosis (MF) have tried to address these issues for patients with suboptimal response to Ruxolitinib therapy. Combination therapies have not been evaluated with Fedratinib so far. Potential combination partners include signaling inhibitors, epigenetic drugs and immunotherapeutics, among others.

The consequences of JAK-inhibition on human immune cell function have been studied in more detail. In early clinical trials, increased numbers of viral infections have been described in MPN patients on treatment with the JAK1/2 inhibitor Ruxolitinib [5, 6]. Moreover, JAK1/2-inhibitors such as Ruxolitinib have been used successfully in rheumatological diseases as well as in the setting of allogeneic transplantation as treatment of acute and chronic graft-versus-host disease (GvHD). In murine models of GvHD Ruxolitinib enhanced survival and limited proinflammatory cytokine production as well as Th1 and Th17 polarization. In MPN patients, JAK1/2 inhibition leads to reduction in CD3 + T-cells and decreased cytokine production. Within the T-cell compartment regulatory T-cells (Treg) and Th1 cells seem to be most prominently affected [7–9]. Also, effector functions of CD8 + T-cells are impaired upon JAK1/2 inhibitor treatment [10]. Furthermore, JAK-inhibition compromises B-cell differentiation and antibody production [11, 12] as well as dendritic cell function [13]. Therefore, it is crucial to determine whether inhibitors targeting JAK1, JAK2, or both could impair T-cell function. JAK1/2 inhibitors as well as JAK2 specific inhibitors had been studied in vitro and in vivo on healthy donor T-cells. Exposure to either JAK1/2 inhibitor resulted in the inhibition of proliferation, global activation (CD69), and STAT1 phosphorylation of CD4 + and CD8 + T-cells, while selective JAK2 inhibition had no such effect. Likewise, when using genetic inactivation of either JAK1 or JAK2 in T-cells only JAK1 depletion was sufficient to inhibit global T-cell function in vitro. JAK2 was dispensable for global T-cell effector functions in mouse models of GvHD. These findings underscore the importance of JAK-selectivity depending on the underlying condition or context. [14]. Consistently, while there were signals for increased rates of infectious complications upon Ruxolitinib treatment in clinical trials, there was no increased incidence in trials using Fedratinib [6, 15–17], with a relatively low rate of infectious complications. These findings indicate that JAK2-specific inhibitors like Fedratinib allows immune responses and therefore may serve as a combination partner for immunotherapeutic agents.

Fedratinib is an oral wild type and mutated Janus Kinase 2 (JAK2) and (FLT3) inhibitor. Fedratinib is JAK2-selective with higher potency for JAK2 over family members JAK1, JAK3 and TYK2. In cell models expressing mutationally active JAK2 or FLT3, Fedratinib reduced phosphorylation of STAT3 and 5 proteins, inhibited cell proliferation, and induced apoptosis. In mouse models of JAK2V617F-driven myeloproliferative neoplasms, Fedratinib inhibited phosphorylation of STAT3/5, increased survival and improved MPN-associated symptoms. This included reduction of white blood cells, hematocrit, splenomegaly, and fibrosis. Fedratinib has been studied extensively in the treatment of patients with myelofibrosis and has recently demonstrated clinical efficacy in a randomized, placebo-controlled, Phase 3 study (JAKARTA) in patients with intermediate-2 or high-risk MF [18, 19].

Most notably, recent reports provided first evidence on how the JAK2-V617F mutated myeloid cells may influence T-cell responses. JAK2-V617F promoted the synthesis of PD-L1 in MPN cells leading to limited anti-neoplastic T-cell responses, metabolic changes in T-cells and eventually JAK2-V617F-driven immune-escape of MPN cells [20]. These findings may facilitate the use of immunotherapeutic approaches for JAK-mutated clones. Immune checkpoints refer to a variety of inhibitory pathways that are crucial for maintaining self-tolerance and modulating the duration and amplitude of physiological immune responses in peripheral tissues in order to minimize collateral tissue damage. Checkpoint inhibitors, such as ipilimumab targeting CTLA-4, pembrolizumab and Nivolumab targeting programmed death-1 (PD-1), have been approved for numerous cancer indications including hematologic malignancies. Nivolumab is one of the most extensively studied immune checkpoint inhibitors across various tumor types. Nivolumab was the first PD-1 immune checkpoint inhibitor to be approved for use in advanced, squamous non-small cell lung cancer (NSCLC) following prior chemotherapy. Nivolumab is a human immunoglobulin G4 (IgG4) monoclonal antibody. It binds to the PD-1 receptor and blocks its interaction with PD-L1 and PD-L2, thus releasing PD-1 pathway-mediated inhibition of the immune response, including the antitumor immune response.

Checkpoint inhibitors Nivolumab and Pembrolizumab have been investigated as monotherapy in patients with myelofibrosis. However, treatment duration was rather short due to the lack of early responses. Of note, immune responses upon checkpoint inhibitor treatment may require a prolonged treatment period to facilitate measurable clinical responses. Upon monotherapy, changes in the immune milieu could still be recorded, further suggesting that a prolonged treatment may facilitate improved responses. Therefore, Fedratinib was a logical combination partner for checkpoint inhibitors as it is an effective JAK-inhibitor to reduce spleen size and symptoms while allowing immune responses over a prolonged period of treatment.

The aim of this phase 2 trial is therefore to evaluate the clinical efficacy of Fedratinib and Nivolumab combination therapy in patients with primary and secondary MF based on the consensus criteria of the International Working Group for Myelofibrosis Research and Treatment (IWG-MRT), extended by the criterion RBC-transfusion independence (RBC-TI).

## Methods

### Study design and objectives

This study is an open-label, single-arm, phase-II trial to assess the efficacy of a drug combination of Fedratinib and Nivolumab in primary (pre-fibrotic or overt) and secondary MF patients with no response or suboptimal response to any JAK-inhibitor therapy (regarding persistence of symptoms, splenomegaly, cytopenia or hyperproliferation) OR failure [secondary resistance] to JAK-inhibitor treatment as defined by IWG-MRT criteria. Dosing regimen of the drugs is derived from previous studies with either Fedratinib or Nivolumab. Fedratinib treatment will be started at 400 mg QD, whereas the dose of Nivolumab will be started in cycle 2 at a fixed dose of 240 mg i.v. every 2 weeks (Fig. 1). Dose adjustment or discontinuation is intended for both drugs in case of severe hematologic and/or non-hematologic toxicity. Treatment cycles are defined as 28 days. The estimated total duration of the study for each patient is 12 months. Patients whose disease responds or who show at least a clinical benefit may continue to receive the combination. Patients will receive study treatment until progressive disease or relapse (acc. to IWG-MRT), death or study discontinuation for other reasons. Both drugs do not have an overlapping toxicity profile as they target distinct biological pathways (JAK2-inhibitor; immune-checkpoint inhibitor). Both classes of compounds have been investigated in phase 2 and 3 trials without excess of toxicity [21–27].

**Fig. 1 Fig1:**
[figure not shown]
Study design. Cycle 1 consists of a run-in phase of Fedratinib monotherapy (400 mg QD) followed by addition of Nivolumab (240 mg Q2wk) from cycle 2 on. Patients will receive study treatment until progressive disease or relapse (acc. to IWG-MRT), death, or study discontinuation for other reasons. Treatment discontinuation will be required upon progression, toxicity or due to patient decision

Primary objective is the evaluation of the clinical efficacy of Fedratinib and Nivolumab combination therapy in primary and secondary MF patients based on the consensus criteria of the International Working Group for Myelofibrosis Research and Treatment (IWG-MRT) [28], extended by the criterion RBC-transfusion independence (RBC-TI) [29, 30]. Secondary objectives include evaluation of the safety of a combination therapy (Fedratinib and Nivolumab) in patients with primary and secondary MF, of the clinical benefit (defined as prolongation of RBC transfusion intervals by ≥ 50% compared to baseline in transfusion dependent patients or ≥ 1 g/dL Hb increase in the absence of RBC transfusion dependency and/or improvement of at least one MF-associated symptom according by at least 50% and/or improvement of ≥ 2 MF-associated symptoms by at least 25%), progression-free survival, response duration, disease burden (allelic ratio of the respective driver mutation and of high-risk mutations by next-generation sequencing [NGS]), fibrosis grade and overall survival, the quality of life / symptom burden by the Myeloproliferative Neoplasm Symptom Assessment Form (MPN-SAF, MPN10) and the adherence using a modified Morisky 8-item questionnaire.

### Study population

The inclusion and exclusion criteria for this study are outlined in Table 1. Major eligibility criteria include adult female and male patients ≥ 18 years of age diagnosed with myelofibrosis (MF) according to the WHO 2008 or 2016 criteria, including primary (pre-fibrotic or overt) and secondary myelofibrosis. The study focuses on patients with an indication for therapy (either symptomatic patients with splenomegaly > 11 cm diameter and/or symptoms restricting their daily activity or patients with DIPSS int-2, or high risk or MIPSS70 int or high). Patients with failure [secondary resistance] to JAK-inhibitor treatment as defined by IWG-MRT criteria can be enrolled as well as patients with no response or suboptimal response to any JAK-inhibitor therapy (regarding persistence of symptoms, splenomegaly, cytopenia or hyperproliferation) defined either by persisting splenomegaly (> 11 cm total diameter), persisting leukoerythroblastosis, anemia < 6.2 mmol/l (< 10 g/dl), elevated WBC (> 11 Gpt/l) or persisting general or constitutional symptoms (persistence is defined as less than 50% reduction to baseline when using the MPN10 TSS Score).

**Table 1 Tab1:** Inclusion and Exclusion Criteria

Inclusion Criteria	Patients must meet **ALL** of the following inclusion criteria to be eligible for enrollment into the study: a. Signed Informed Consent Form available b. Patients* ≥ 18 years of age c. Patients diagnosed with myelofibrosis (MF) according to the WHO 2008 or 2016 criteria, including primary (pre-fibrotic or overt) and secondary myelofibrosis d. Patients with an indication for therapy (either symptomatic patients with splenomegaly > 11 cm diameter and/or symptoms restricting their daily activity or patients with DIPSS int-2, or high risk or MIPSS70 int or high) e. Patients with no response or suboptimal response to any JAK-inhibitor therapy (regarding persistence of symptoms, splenomegaly, cytopenia or hyperproliferation) defined either **by ANY ONE of the following criteria** (f-k): f. Persisting Splenomegaly > 11 cm total diameter g. Persisting leukoerythroblastosis h. Anemia < 6.2 mmol/l (< 10 g/dl) i. Elevated WBC (> 11 Gpt/l) j. Persisting general or constitutional symptoms (persistence is defined as less than 50% reduction to baseline when using the MPN10 TSS Score) **OR** k. failure [secondary resistance] to JAK-inhibitor treatment as defined by IWG-MRT criteria l. ECOG performance status < 3 at screening and adequate organ function m. Reliable contraception should be maintained throughout the study and for 1 month after discontinuation of Fedratinib or 5 months after discontinuation of Nivolumab** n. Subject must be willing to receive transfusion of blood products o. Thiamine levels not below lower limit of normal (prior substitution is possible) p. Normal nutritional status, as judged by the physician q. Females of childbearing potential (FCBP) must undergo repetitive pregnancy testing (serum or urine) and pregnancy results must be negative r. Unless practicing complete abstinence from heterosexual intercourse, sexually active FCBP must agree to use adequate contraceptive methods (i.e. failure rate of < 1% per year) s. Males (including those who have had a vasectomy) must use barrier contraception (condoms) when engaging in sexual activity with FCBP. Males must agree not to donate semen or sperm *There are no data that indicate special gender distribution and the risk to be diagnosed with myelofibrosis (MF) does not depend on a patient’s gender. Therefore, patients will be enrolled in the study gender-independently
Exclusion Criteria	The presence of **ANY** of the following criteria will exclude a patient from study enrollment: a. Planned hematopoietic stem cell transplantation within 3 months and suitable donor available b. > 10% blasts in bone marrow smear (cytology) or > 2 × in blood smear within the screening phase or > 20% blasts at any time in bone marrow or peripheral blood smears c. Creatinine > 2xN and Creatinine-Clearance < 45 ml/min; ALAT, ASAT & bilirubin > 3xN (if MF impact on liver > 5xN) d. Baseline platelets count below 50 × 10^9^/L and ANC < 1.0 × 10^9^/L e. Diagnosis of PV, ET (according to WHO 2016) or positive molecular test for BCR-ABL f. Patients on ongoing medication for myelofibrosis including systemic corticosteroids (detailed list of permitted medications is provided in paragraph 9.1.10.4 and Appendix V). Use of steroids within 14 days prior to the first dose of study drug and until end of treatment is prohibited by patients g. Uncontrolled infection h. Evidence of acute or chronic infection with hepatitis B, hepatitis C, human immunodeficiency virus (HIV) or tuberculosis i. Current participation in any other interventional clinical study within 30 days before the first administration of the investigational product or at any time during the study, unless it is an observational (non-interventional) study, or during the follow-up period of an interventional study with last dose of investigational product ≥ 30 days prior first administration of investigational product within this study j. No consent for registration, storage and processing of the individual disease characteristics and course as well as information of the family physician about study participation k. No consent for biobanking of patient’s biological specimens l. Prior therapy with checkpoint-inhibitors m. Vaccination within 4 weeks prior to treatment start n. Hypersensitivity to the IMPs or to any of the excipients o. History of or uncontrolled autoimmune disease such as autoimmune-hepatitis, -pneumonitis, -thyroiditis, chronic inflammatory bowel disease, multiple sclerosis, or rheumatologic diseases (including but not limited to systemic lupus and vasculitis) p. History of malignancy except for i) adequately treated local basal cell or squamous cell carcinoma of the skin, ii) asymptomatic prostate cancer without known metastatic disease and with no requirement for therapy or requiring only hormonal therapy and with normal prostate-specific antigen for ≥ 1 year prior to randomization, or iii) any other cancer that has been in complete remission for ≥ 5 years q. Secondary malignancy that limits survival to less than 6 months r. Drug or alcohol abuse within the last 6 months s. Patients who cannot adhere to the Pregnancy Prevention Plan t. Pregnant or breast-feeding females u. Thiamine levels below normal limit despite supplementation v. Patients who are unable to consent because they do not understand the nature, significance and implications of the clinical trial and therefore cannot form a rational intention in the light of the facts [§ 40 Abs. 1 S. 3 Nr. 3a AMG]

### Study drugs

Fedratinib capsules will be administered orally, QD, 400 mg (100 mg capsules will be provided: 4 capsules of 100 mg per day). Fedratinib treatment will be administered as a run-in phase for 4 weeks. Fedratinib dose modifications will be allowed based on observed toxicity to a 300 mg or 200 mg, or 100 mg daily dose or may be temporarily discontinued in this study. For the first 2 cycles, a fixed dose of 400 mg should be maintained with appropriate supportive medication, as major toxicities have been shown to decrease with increasing number of treatment cycles [31]. Provisions are in place to allow further dose reduction for subjects with co-medication with moderate or strong Cytochrome P4503A4 (CYP3A4) inhibitors.

From cycle 2 on, Nivolumab will be added at a fixed dose of 240 mg i.v., every 2 weeks. The frequency of Nivolumab infusion can be reduced based on observed toxicity. Infusions can be continued even if Fedratinib is temporarily discontinued.

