The fact that patients had no relevant responses regarding spleen size and symptom burden may have contributed to their early discontinuation and drop out (Supplementary Table S2). The combination of checkpoint-inhibitors with the first available JAK-inhibitor Ruxolitinib is not possible due to its efficacy on JAK1 leading to impairment of T-cell function. However, Fedratinib, a JAK2-specific compound, has shown to allow immune responses in pre-clinical and clinical settings. This enables a therapeutic window to explore the induction of immune responses by the established checkpoint-inhibitor Nivolumab in combination with the selective JAK2-inhibitor Fedratinib. Checkpoint-inhibitors mediate indirect anti-tumor activity by activating T-cell responses. While Nivolumab can eradicate malignant MPN cells through activation of T-cell responses, Fedratinib predominantly reduces the spleen size and improves constitutional symptoms. As both aspects of disease control are highly relevant and addressing clinical needs in MF, the combined use of the drugs provides a promising therapeutic concept. Therefore, the risk–benefit ratio is based on arguments discussed above and clearly favors to the beneficial side.

The sequential administration of both drugs is poised to mitigate adverse effects: the initiation of Fedratinib dosing at baseline affords patients the opportunity to acclimate to the treatment and mitigate potential gastrointestinal (GI) toxicity. Notably, GI toxicity is the most common adverse event observed with Fedratinib treatment, as elucidated by England and colleagues [40]. However, its incidence can be significantly attenuated with concurrent interventions such as anti-emetic prophylaxis or standby anti-diarrhea medication like loperamide. Remarkably, while diarrhea manifested in up to 80% of patients during the early Fedratinib trials, the implementation of supportive medication regimens in the FREEDOM trials substantially reduced these side effects to below 40% [40].

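### The article's fixed 400 mg fedratinib dose for cycles 1 and 2, and the ungraded discontinuation in its Fig. 1 legend, are not reconciled with its own rules on modification for toxicity

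*Protocol article*

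**What the plan says.** Three places in the protocol article tell the reader what happens to treatment when toxicity occurs.

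- **Methods, Study drugs.** One sentence permits modification: "Fedratinib dose modifications will be allowed based on observed toxicity to a 300 mg or 200 mg, or 100 mg daily dose". It adds that the drug "may be temporarily discontinued in this study". It names no cycle and no grade. The next sentence reads "For the first 2 cycles, a fixed dose of 400 mg should be maintained with appropriate supportive medication" and gives as its reason that major toxicities become less frequent as cycles accumulate. On the second drug, the section says "From cycle 2 on, Nivolumab will be added at a fixed dose of 240 mg i.v., every 2 weeks".
- **Methods, Study design and objectives.** "Dose adjustment or discontinuation is intended for both drugs in case of severe hematologic and/or non-hematologic toxicity". Cycles 1 and 2 are not excepted. This section also sets the cycle length at 28 days.
- **Fig. 1 legend.** "Treatment discontinuation will be required upon progression, toxicity or due to patient decision". No grade is attached to toxicity, and neither drug is named.

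**The concern.** The instruction to keep 400 mg for two cycles and the permission to reduce or interrupt for toxicity stand in adjacent sentences. Nothing says which gives way when both apply. The general severe-toxicity rule in Study design and objectives does not mention the two-cycle window, and the window sentence does not mention that rule. The legend then uses mandatory language for an event that the other two places treat as open to graded responses.

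The question matters most early on. Nivolumab joins in cycle 2, so the fixed-dose window includes the first cycle on both drugs, and the Introduction says that combinations with fedratinib have not been evaluated before. Safety of the combination is a secondary endpoint. A reader of the eventual safety results needs to know which rule governed dose changes and discontinuations in those weeks.

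**Working it through.** The article gives no figure to reproduce on this point, and no sample size, power or event rate enters. The check is the calendar and a side-by-side reading.

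**Timing.** Inputs: cycle length of 28 days (Study design and objectives), a fixed-dose window of 2 cycles and nivolumab from cycle 2 (both Study drugs).

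- Length of the window: 2 × 28 = 56 days.
- Cycle 2 runs from day 28 + 1 = 29 to day 56, so 56 − 28 = 28 days of the window, half of it, are planned on both drugs.

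**Side by side.**

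| Place | Direction | Severity condition | Cycle condition |
|---|---|---|---|
| Study drugs, modification sentence | Reduction or temporary interruption allowed | Observed toxicity, no grade | None |
| Study drugs, fixed-dose sentence | 400 mg kept, with supportive medication | No exception stated | Cycles 1 and 2 |
| Study design and objectives | Adjustment or discontinuation intended, both drugs | Severe | None |
| Fig. 1 legend | Discontinuation required | Toxicity, no grade | None |

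**Case 1: severe toxicity in cycle 1 or 2.** All four rows apply as worded. The second row points to keeping the dose, the first and third to changing or stopping it, and the fourth to stopping. No row states that it overrides another.

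**Case 2: toxicity that is not severe, in any cycle.** The first row allows a lower dose or an interruption. The fourth, read literally, requires discontinuation. Study drugs also lets nivolumab infusions continue while fedratinib is interrupted, so the article clearly foresees toxicity that does not end treatment. The legend's wording leaves no room for it.

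**Can the fixed-dose sentence be confined to mild toxicity?** Its own reason speaks against that. It appeals to the decline of major toxicities over time, so it has substantial toxicity in view. The article does not separate major toxicity, the term in Study drugs, from severe toxicity, the term in Study design and objectives. A reader cannot tell where the one instruction ends and the other begins.

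**The case against.** The strongest reply is that this is a condensed article. Sites treat from the full protocol (Version 4.0 under Trial status), and graded modification tables belong there. The article itself sends withdrawal conditions to a supplementary figure that is not shown. The wording is also soft: the fixed dose *should* be maintained, modification is *allowed*, adjustment is *intended*. The statements can be read as steps: support the dose early, modify for toxicity, adjust or stop if it is severe. The legend sentence follows one on how long patients stay on treatment and may be only a short list of reasons for ending it.

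Much of this stands. The absence of grade tables is no finding. What remains is that printed sentences give different directions for the same event. Reading them as steps also needs a link between severity and action that the fixed-dose sentence and the legend do not supply.

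A reader might infer more than the documents support:

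- *Three incompatible rules.* Study design and objectives and the modification sentence largely agree. The conflict lies with the fixed-dose sentence and the legend.
- *Sites cannot apply one rule.* This is not shown, because the document that sites use is not at hand.
- *A second conflict over co-medication.* "Provisions are in place to allow further dose reduction for subjects with co-medication with moderate or strong Cytochrome P4503A4 (CYP3A4) inhibitors" follows directly after the fixed-dose sentence and reads naturally as an exception to it, with details held elsewhere.
- *Clashing rationales.* The Discussion says "the initiation of Fedratinib dosing at baseline affords patients the opportunity to acclimate to the treatment", and Study drugs says that major toxicities decline over cycles. Both mean that tolerability improves with time on the drug.
- *A count of affected patients.* The Discussion's diarrhoea figures would give 0.40 × 30 = 12 to 0.80 × 30 = 24 patients. The 80% figure comes from earlier trials, not from early in treatment, and predates the supportive medication that the fixed-dose sentence calls for. The later figure is below 40%, so 12 would be a ceiling. Neither figure has an onset time or a severe share.
- *A shift in the response count.* Nothing in the article lets one derive it.

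**Conclusion.** The point holds in a narrow form. The fixed-dose sentence has no stated exception for severe toxicity and is not reconciled with the modification sentence before it or with the severe-toxicity rule in Study design and objectives. Separately, the Fig. 1 legend requires discontinuation for toxicity of unstated severity, against a text that allows reduction and interruption. This is a contradiction between stated rules and not merely missing detail.

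Its size can be given only as time: 56 days per patient, of which days 29 to 56 are the first combined exposure. That figure marks when the conflict can arise and does not measure harm. The conclusion rests on the article as printed and assumes nothing about what the full protocol or the supplementary figure says. If they settle the matter, the defect is confined to the published account. It merits correction in either case, because it concerns how severe toxicity is handled during first exposure to an untested combination.

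**What to change.** Reconcile Study design and objectives, Study drugs and the Fig. 1 legend with one another and with Version 4.0 of the protocol. The reconciled text should state:

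1. whether the fixed dose in cycles 1 and 2 yields to the severe-toxicity rule;
2. which toxicity leads to modification or interruption, and which to required discontinuation;
3. which drug the legend's discontinuation refers to.

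Which rule applies is for the sponsor and its safety reviewers to decide, and this review takes no position on it.

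The first step is to check Version 4.0. If it already answers these questions, the article needs corrected wording only. If it has the same gap, the protocol needs the same clarification, sent to the 9 centers. Neither route needs extra patients, procedures or analyses. As of May 2024, 23 of 30 patients had entered, so any clarification would govern later entrants and the reporting of all patients.
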